# Study Size

A purposeful convenience sample will be employed for this trial owing to the feasibility nature and the contingent sequential recruitment model described. These factors together make it impractical for a formal sample size calculation to be attended.

This trial will intend to recruit 160 total participants across 8 groups of 20 possible participants with acknowledgement that the total number of recruited participants is dependent on the outcome of the serial assessments in each group. Recruitment will be shared equally between the traditional face to face CPR training group and the hybrid sessions based on the video training aid. Each group will be randomised to either the traditional face to face or hybrid groups electronically with the assignment being concealed in an opaque envelope which will be opened immediately prior to the commencement of the session.

While all efforts to maximise recruitment to ensure full groups of 20 will be taken, it is acknowledged that there may be attrition leaving some groups slightly short of the 20 participants. These details and reasons for the shortages will be reported along with the trial findings.

# Statistical Methods

The primary analysis method will follow the intention to treat principles. Differences between each of the 2 active cohorts (intervention arm, Hybrid CPR Training, and the control arm, Traditional CPR Training), will be assessed using a binomial test of proportions, with 95% confidence intervals for the difference presented together with the p value for the difference. A two-sided 90% confidence interval (equivalent to a 95% one sided interval) will be estimated for the difference in successful assessments between two different training teams. If the upper limit of this interval is < 0.15 the hybrid CPR Training arm will be declared non-inferior. Continuous secondary outcomes will be compared between groups using ANOVA models.

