# Trial Design

This study will utilise a prospective cohort design to evaluate the feasibility of peer facilitated CPR training provided by community members following either A) a traditional face to face CPR training session OR B) a hybrid model based around a simple video-based training aid.

Groups of 20 participants will be recruited to participate in this study through Hunter Heart Safe training sessions. These larger groups will then be further broken down into 5 ‘streams’ of 4 participants. The first participant in each of the streams (generation 1) will be designated to receive either traditional face to face CPR training OR a hybrid training session based around a simple video-based training aid. The participants will be randomized to either one of the two arms of training blocks based on a computer generated randomized sequence. The four participants following on from the initial trainee in each ‘stream’ are referred to as subsequent ‘generations’ i.e. the second person in a stream constitutes the second generation of that stream, the fourth person in sequence is the fourth generation etc.

Following on from their initial training, the first participants from each stream will then be tasked with teaching the lesson they have learned (one on one) to the second generation. If this message is conveyed successfully, the second generation will be tasked with teaching the third, and so on until either the message fails to be delivered appropriately, or all 4 generations within a single stream have been successfully taught CPR.

***
[figure not shown]
***

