***Graphical Representation of the Study Design***

Following training of the initial participants, peer to peer training within each stream will be attended in separate rooms to avoid cross communication where possible. Once an individual has successfully delivered their training to the next generation in their stream, that person will have completed their participation in the trial. At the completion of the data collection period, a final large group session of conventional CPR training will be offered to all participants as a way of ensuring suitable validated training is offered to all participants.

For one generation to progress from learning to teaching, they must successfully complete an assessment against a ‘critical item checklist’ (as outlined in appendix C). The first generation will be excepted from this assessment as the initial the initial training sessions efficacy is not the primary focus of this trial. If the participant passes this assessment, they are instructed to teach the participant in the next generation of their stream what they have learned over a 20-minute period. If any member of the stream fails the assessment, data collection for that stream ends and all remaining members of that stream are deemed to have completed their participation in this trial. An assessment must be completed by every generation involved in peer facilitated teaching.’

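### Whole sessions are randomised (4 per arm), but the binomial test and its intervals treat single CPR assessments as independent, so they are too narrow by an amount the protocol does not let one fix

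*Protocol*

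**What the plan says.** **Allocation.** Study Size is specific about the unit: "Each group will be randomised to either the traditional face to face or hybrid groups electronically". The assignment is concealed in an envelope opened just before the session. The same section gives the numbers: "This trial will intend to recruit 160 total participants across 8 groups of 20 possible participants" and "Recruitment will be shared equally between the traditional face to face CPR training group and the hybrid sessions". That is 4 groups per arm. Trial Design is looser: "The participants will be randomized to either one of the two arms of training blocks based on a computer generated randomized sequence".

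**Structure within a group.** Trial Design: "These larger groups will then be further broken down into 5 ‘streams’ of 4 participants". A learner who passes teaches the next person in the stream, and under Graphical Representation of the Study Design, "If any member of the stream fails the assessment, data collection for that stream ends". Generation 1 is not assessed, so a stream yields at most 3 assessments.

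**Analysis.** Under Statistical Methods, the two arms "will be assessed using a binomial test of proportions, with 95% confidence intervals for the difference presented together with the p value for the difference". Non-inferiority is then decided by setting a 90% interval (two-sided) for the difference in successful assessments against 0.15. The protocol nowhere mentions clustering by group, a design effect or a group-level analysis. Outcomes describes the measure as a raw number of successful assessments and states no denominator.

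**The concern.** A two-sample binomial comparison assumes that every assessment is an independent trial. Here a whole session receives one allocation, and its members share the occasion and the venue and often come from the same community group. The sections Study Setting and Participants show that venues and recruitment sources will differ between sessions. Any difference in pass rate between sessions enters the difference between arms, and the binomial standard error has no term for it. With 4 sessions per arm, such differences do not average out well.

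The p value, the 95% interval and the 90% interval are all affected. A chance imbalance between a few sessions could be reported as an effect of the training format, or hybrid training could be declared non-inferior on an interval narrower than the design supports.

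**Working it through.** **Inputs from the protocol**
- 8 groups x 20 = 160 participants, which reproduces the planned recruitment. This is the only size figure; there is no power calculation to reproduce.
- Per arm: 4 groups, 20 streams, and at most 20 x 3 = 60 peer-taught assessments.
- Test: two-sided 5%. Non-inferiority: 90% interval, margin 0.15.

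**Inputs assumed, because the protocol gives none**
- Per-step pass rate p of 0.5 to 0.9, the same in both arms.
- Standard deviation of group pass rates on the logit scale of 0, 0.2, 0.4 or 0.8. At p = 0.7 (logit 0.847), one standard deviation either side of the average spans pass rates of about 0.66 to 0.74, 0.61 to 0.78 and 0.51 to 0.84 for the three non-zero values.

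**Step 1. The chain alone, planned denominator (60 per arm, unreached learners counted as not successful).** The number of successes S in a stream takes the values 0, 1, 2, 3 with probabilities 1-p, p(1-p), p²(1-p), p³. At p = 0.7:
- E(S) = 0.7 + 0.49 + 0.343 = 1.533, so the proportion is 1.533/3 = 0.511.
- Var(S) = 1.535; binomial variance = 3 x 0.511 x 0.489 = 0.750; ratio = 2.05.
- Actual size of a nominal 5% two-sided test = 2 x [1 - Φ(1.96/√2.05)] = 0.171.
- Actual size of a nominal 5% one-sided test = 1 - Φ(1.645/√2.05) = 0.125.

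| p | variance ratio | two-sided error | one-sided error |
|---|---|---|---|
| 0.5 | 1.79 | 14% | 11% |
| 0.7 | 2.05 | 17% | 13% |
| 0.9 | 2.25 | 19% | 14% |

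**Step 2. The chain alone, performed denominator.** Given the past, each attempted step is a single trial with probability p, so stopping at the first failure adds almost nothing. Simulated two-sided error is 4.9% to 5.6%.

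**Step 3. Adding variation between groups (simulation, 4 groups x 5 streams x up to 3 assessments per arm, no true difference).**

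| group SD (logit) | two-sided error, performed | two-sided error, planned |
|---|---|---|
| 0 | about 5% | 14% to 19% |
| 0.2 | about 6% | between the rows above and below |
| 0.4 to 0.8 | 7% to 9% at 0.4; 13% to 18% at 0.8 | about 21% to 33% |

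A t test on the 4 v 4 group proportions stays between about 4.4% and 5.6% throughout.

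**Step 4. Cross-check by formula.** At p = 0.6 the expected number performed per stream is 1 + 0.6 + 0.36 = 1.96, so 39.2 per arm and about m = 10 per group. The design effect is 1 + (m-1) x ICC. For assumed ICCs of 0.01, 0.05 and 0.10 it is 1.09, 1.45 and 1.90, and 2 x [1 - Φ(1.96/√DE)] gives 6.1%, 10.4% and 15.5%. Simulation at those ICCs, performed denominator, gives 6.4%, 11.1% and 15.6%.

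**Step 5. Interval width at p = 0.7 with no group effect (90% half-width).**
- Planned, binomial: 1.645 x √(2 x 0.511 x 0.489/60) = 1.645 x 0.0913 = 0.150.
- Planned, group level: 1.943 x 0.0913 x √2.05 = 1.943 x 0.131 = 0.254.
- Performed, binomial: expected number per arm 20 x (1 + 0.7 + 0.49) = 43.8; 1.645 x √(2 x 0.7 x 0.3/43.8) = 0.161.
- Performed, group level: 1.943 x 0.0979 x 1.03 (simulated ratio of true to binomial standard error) = 0.196, about 0.20.

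Moving from the normal quantile to t on 8 - 2 = 6 degrees of freedom widens the 90% interval by 1.943/1.645 = 1.18, even with no variation between groups.

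**The case against.** **The size is assumed.** The protocol gives no pass rate and no measure of variation between groups. With little variation (SD 0.2) and performed assessments, the error is about 6%, hardly more than nominal. This stands, and it limits what can be said about size. It does not rescue the method, since taking the variation between sessions as zero has no support in the protocol either.

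**The chain need not matter.** A reader might infer that independence fails with serious effect at both levels, group and stream, and that the intervals are far too narrow whatever the details. The protocol does not support that. The near-doubling of variance appears only if learners who were never reached count as failures. Counting successful assessments, with data collection ending at a failure, is at least as natural a reading. Intention to treat leaves the other one open.

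**The unit of randomisation is not uniform.** Trial Design speaks of participants being randomised. The Study Size wording is more specific, with an assignment concealed for each group and opened at its session, and this point relies on it.

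**ANOVA.** A reader might extend the criticism to "Continuous secondary outcomes will be compared between groups using ANOVA models". Outcomes names no continuous outcome, and an ANOVA model can include group as a nested factor, so no error is shown there.

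**Scope.** The primary outcome is a count across all groups and needs no test between arms. The comparison serves the secondary outcome of a feasibility study with a convenience sample. That tempers the consequences, but a p value and a formal non-inferiority declaration are still planned.

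**A separate analysis plan.** One may exist, but the protocol itself names the test, so this is not a detail left open.

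**Conclusion.** The point holds. The allocation is by group, 4 per arm, and the named test, its p value and both intervals ignore that. The direction is clear: p values too small, intervals too narrow. The amount is conditional:
- On performed assessments it ranges from slight (about 6% error) to substantial (13% to 18%) over the assumed group SDs of 0.2 to 0.8.
- On 60 planned assessments per arm it is large even without group variation (14% to 19%).

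The protocol does not settle which case applies. A flat statement that the intervals are far too narrow, or that the chain by itself invalidates the test, would go beyond it. These figures assume a common per-step pass rate of 0.5 to 0.9 and group-level allocation as Study Size describes. The correction should be made before the analysis, because the non-inferiority decision depends directly on interval width.

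**What to change.** In Statistical Methods, replace the binomial test with an analysis of the 8 group results on the scale of the 0.15 margin:
1. State the denominator: assessments performed, or all planned peer-taught assessments with unreached learners counted as not successful.
2. For each group compute the proportion of successful peer-taught assessments. With the planned denominator this is the mean number of generations passed per stream divided by 3. An undivided 0 to 3 mean would not be on the scale of the margin.
3. Compare the 4 v 4 group proportions with a t-based 95% interval on 6 degrees of freedom. Support it with the exact permutation test over the 70 possible equal allocations, whose smallest two-sided p value is 2/70 = 0.029.
4. Take the 90% interval for the non-inferiority rule from the same group-level analysis.
5. Align the randomisation sentence in Trial Design with Study Size.

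The cost is wording and very little analysis work; recruitment and conduct stay as they are. The drawback is wider intervals. At a pass rate of 0.7 with no group effect, the 90% half-width goes from about 0.15 to about 0.25 (planned) or from about 0.16 to about 0.20 (performed). Each of these group-level half-widths exceeds 0.15, so at that pass rate non-inferiority could be declared only if the observed difference favoured hybrid training.

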# Data Management

All data collected will be compiled via Redcap (*electronic survey software*). At the conclusion of the data collection period, the Redcap data will be exported in a spreadsheet which will then be stored on a central computer as well as a backup portable hard drive. Both the main study computer and backup hard drive will be password protected.

Hard copies of the critical item checklists used to mark the CPR assessments between generations will be scanned and stored on a central computer as well as a backup portable hard drive. The results of these checklists will also be added into a separate section of the spreadsheet containing the Redcap data for the purpose of data analysis.

# Harms

As only simulated patients will be used in this trial there will be no potential to cause harm to any living patient. The primary risk associated with this study is the potential for participants to receive substandard CPR training leading to a propagation of incorrect teaching within the wider community. Two measures are in place to control this risk:

1. Within each stream being examined, the progression of the peer-to-peer teaching will be ceased when a participant fails to achieve all items on the critical item checklist
2. At the end of each session, regardless of the group allocation, all groups will be offered standard group training delivered in a traditional face to face capacity by the Hunter Heart Safe Trainers (*this will be after all data has been collected so as to not confound the results of the study*)

# Auditing

As this is a small-scale trial in which the investigators will be directly overseeing the intervention and data collection there is no benefit in instituting procedures guiding the auditing of trial conduct.

# Research Ethics Approval

This trial will be submitted to the Hunter New England Human Research Ethics Committee for a relevant review.

# Consent or Assent

Informed consent will be gained from all participants before they partake in the trial. Members of the study group (*investigators*) will be responsible for ensuring that participants are adequately informed about the trial. This will involve a verbal briefing as well as the delivery of a participant information sheet to all prospective participants.

- A copy of the participant consent form used for this trial is attached as *appendix A*.
- A copy of the participant information form is attached as *appendix B*.

# Confidentiality

Any personal information collected during the course of this trial will be maintained in the confidence of the study group (*investigators*). No personal information will be shared outside of this group at any stage during the course of the trial.

Any clinical or practical data collected during the course of this trial will be maintained in the confidence of the study group while the project is ongoing. When the data are analysed and prepared for publication all personal identifiers will be removed.

# Declaration of Interests

The investigators involved in this trial are involved in the coordination of and training provided by the Hunter Heart Safe Group. This group is not for profit. There are no financial incentives or otherwise confounding interests to declare.

# Access to Data

The final study dataset will be available to all listed study contributors at completion of the data collection period. Upon completion of the data collection period, the data will be analysed and prepared for publication. Once the final data analysis is completed and the findings of this trial have been submitted for publication, the final trial data set will be made available to external parties upon request at the discretion of the principal investigator.

# Ancillary and Post-Trial Care

All participants will be able to contact the study group if additional information or support is required following their participation in this trial. All participants in this trial will be given a certificate of participation.

# Dissemination Policy

Following final analysis, the findings of this trial will be compiled and submitted for potential publication in a selected emergency medicine journal. All authors will collaboratively produce a final manuscript outlining the findings of this trial.

Once the final data analysis is completed and the findings of this trial have been submitted for publication, the final trial data set, protocol and statistical code used will be made available to external parties upon request at the discretion of the principal investigator.

